### Statistical methods

Given the exploratory nature of the trial, analyses will be descriptive. Changes in lesion count, SUV_max_ and SUV_mean_ will be summarised using medians and IQRs. Comparative analyses between the scans performed on day 7 or 14 will be compared with baseline may use the Wilcoxon signed-rank or linear mixed models where appropriate. Results will guide power calculations for subsequent confirmatory trials.

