**Methods and analysis:**

The DARO-flare trials are a prospective, single-centre, interventional, phase I–II proof-of-concept study evaluating whether short-term administration of darolutamide induces a PSMA-flare in patients with hormone-sensitive PCa. The cohort being investigated comprises patients with oligometastatic recurrence following prior therapy with curative intent.

Within the cohort, participants are randomised (1:1) to receive darolutamide 600 mg two times a day for either 7 or 14 days. All participants undergo baseline PSMA positron emission tomography (PET)/CT imaging as standard-of-care and two follow-up scans on days 7 and 14.

The primary endpoint was the change in the number of PSMA-expressing PCa lesions and/or PSMA expression per lesion maximum standardised uptake value on repeated PSMA PET/CT, indicative of a darolutamide flare response. Secondary endpoints included the impact on clinical management decisions, defined as a treatment change following short-course darolutamide, tolerability and toxicity as assessed by adverse event reporting, and patient-reported outcomes related to quality of life.

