### Population and eligibility criteria

The study population comprises patients diagnosed with PCa, with oligometastatic recurrence (≤5 lesions) detected on re-staging PSMA PET/CT following curative-intent treatments like robot-assisted radical prostatectomy (RARP) or external beam radiation therapy (EBRT). Baseline staging before definitive treatment was performed according to standard clinical practice. Histopathological characteristics, including histological subtype, are recorded in the electronic patient record.

Inclusion criteria require participants to be adult men (>18 years), with histologically confirmed PCa, an Eastern Cooperative Oncology Group performance status of 0–1, and a life expectancy exceeding 12 months. Patients must not have received prior hormonal therapy, must be able to understand the patient information form, and must have provided written informed consent. In addition, eligible patients must have previously undergone RARP or EBRT, and have a PSMA PET/CT demonstrating 1–5 metastatic lesions in bones and/or lymph nodes, irrespective of prostate-specific antigen (PSA) level, grade or disease stage.

Exclusion criteria include non-adenocarcinoma histology, prior PSMA-based radioligand therapy, prior use of ARTAs within the preceding 3 months, presence of visceral or central nervous system metastases, concurrent cytotoxic chemotherapy, immunotherapy, radioligand therapy or investigational therapy, and other specified medical conditions that could impact trial participation (see Concomitant medication section). Additional exclusions include known hypersensitivity to darolutamide or related compounds, prior hip replacement surgery, Sjogren’s syndrome, the presence of second active malignancies or unwillingness to use medically acceptable forms of barrier contraception.

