### Objectives

The primary endpoint was to prospectively investigate whether the ‘darolutamide flare phenomenon’, observed after the administration of the second line ARTA darolutamide in patients with PCa, results in (1) a higher number of PSMA expressing PCa deposits, either defined as local residual disease or metastatic disease, or (2) in a higher expression of PSMA in individual lesions, determined by SUV_max_, on PSMA PET/CT.

The secondary objectives were (1) to assess the absolute number and the relative number of patients in whom a treatment change is observed by renewed imaging by PSMA PET/CT after a short (7 or 14 days) course of administration with darolutamide, and (2) to assess the patient-reported toxicity and side effects of a short course of administration with darolutamide.

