### Sample size

A total of 16 patients will be enrolled, with eight participants per treatment arm (figure 1). The decision to include eight patients per study group is based on a confidence level of 95% and an estimated event probability of 32%, derived from prior studies reporting an average PSMA upregulation of approximately 40% (95% CI 1% to 110%). This sample size is pragmatic and aligns with typical early proof-of-concept oncology studies, focusing on biological feasibility rather than hypothesis testing. Data generated from this study will inform statistical powering of future randomised trials.

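### The SUV endpoint is per lesion and patients bring one to five lesions, yet the plan permits a signed-rank test without fixing the unit of analysis; pooling lesions would overstate the evidence.

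*Protocol article*

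**What the plan says.** The Objectives section of the protocol article asks, as the second part of the primary question, whether the flare results "in a higher expression of PSMA in individual lesions, determined by SUV_max_, on PSMA PET/CT". The abstract (Methods and analysis) gives the primary endpoint as the "change in the number of PSMA-expressing PCa lesions and/or PSMA expression per lesion maximum standardised uptake value". For SUV, then, the unit named is the lesion. No SUV value per patient is defined.

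Under Population and eligibility criteria, patients must "have a PSMA PET/CT demonstrating 1–5 metastatic lesions in bones and/or lymph nodes". Sample size counts patients: "A total of 16 patients will be enrolled, with eight participants per treatment arm".

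Statistical methods calls the analyses descriptive. It summarises changes in lesion count, SUVmax and SUVmean by medians and IQRs, and adds that day 7 or day 14 comparisons with baseline "may use the Wilcoxon signed-rank or linear mixed models where appropriate". It does not say whether medians, IQRs or tests are taken over patients or over lesions. It ends by saying that the results will feed power calculations for later confirmatory trials.

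**The concern.** A signed-rank test treats each paired difference as independent. Lesions in one patient share the drug exposure, the injected activity, the uptake time and the scan session, so their changes from baseline are likely to be correlated. If the test is applied to the endpoint as it is worded, with the lesion as the pair, the information is counted several times over and the p-value is too small.

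A pooled summary has a related fault. A patient with five lesions gets five times the weight of a patient with one, so the median describes the average lesion and leans towards patients with more disease.

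At stake are the p-values that the article allows to be reported for its primary endpoint, and the variability estimates meant for the next trial.

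**Working it through.** **The plan's own figure.** Eight patients per arm is "based on a confidence level of 95% and an estimated event probability of 32" per cent. The formula is not named, but one reading reproduces it: the number needed to see at least one event with 95% probability is ln(0.05)/ln(1 − 0.32) = 7.77, rounded up to 8. Check: 1 − 0.68^8 = 0.954, and 1 − 0.68^7 = 0.933. On this reading the design counts patients, while the SUV endpoint counts lesions.

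**Inputs from the article.** There are 8 patients per arm, 16 in all, with 1–5 lesions each. Each scan comparison therefore has between 16 × 1 = 16 and 16 × 5 = 80 lesion pairs, from 16 patients.

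**Assumptions, because the article gives no figure.** The level is a nominal two-sided 5%. The intra-patient correlation (ICC) of lesion changes is varied from 0.1 to 0.8. Three spreads of lesion counts are used: equal shares of 1, 2, 3, 4 and 5; mostly few (50%, 25%, 12%, 8% and 5% for 1 to 5 lesions); and five in every patient.

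**Design effect.** For unequal cluster sizes m it is 1 + (E[m²]/E[m] − 1) × ICC.
- Equal shares: E[m] = 3 and E[m²] = (1 + 4 + 9 + 16 + 25)/5 = 11, so the factor is 11/3 − 1 = 2.67. The design effect is 1.8, 2.3 and 2.9 at ICC 0.3, 0.5 and 0.7.
- Mostly few: E[m] = 1.93 and E[m²] = 5.11, so the factor is 1.65. The design effect is 1.5, 1.8 and 2.2.
- Five in every patient: the factor is 4. The design effect is 2.2, 3.0 and 3.8.

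**Type I error by simulation.** The signed-rank test was run on pooled lesions under no mean change, with normal patient effects plus lesion error and 4,000 trials per cell. The pair of figures is for 8 and 16 patients.

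| ICC | Mostly few | Equal shares 1–5 | Five in every patient |
|---|---|---|---|
| 0 | 4.8%, 5.2% | 5.0%, 4.8% | 4.0%, 4.8% |
| 0.1 | 5.8%, 6.3% | 7.8%, 8.4% | 9.2%, 8.7% |
| 0.3 | 9.2%, 10.2% | 14.1%, 14.2% | 18.0%, 18.3% |
| 0.5 | 13.9%, 14.4% | 20.0%, 19.2% | 26.0%, 25.2% |
| 0.8 | 18.4%, 18.7% | 28.2%, 26.0% | 33.5%, 33.8% |

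The simulation error at a true 5% is √(0.05 × 0.95/4000) = 0.3 percentage points. With one lesion in every patient the rate was 3.3–5.4%. With one median change per patient it was 3.7–5.3% in every multi-lesion setting.

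**Cross-check by formula.** If the standard error is too small by √(design effect), the two-sided error is about 2 × [1 − Φ(1.96/√design effect)].
- Equal shares, ICC 0.3: 1.96/√1.80 = 1.46, giving 14%.
- Equal shares, ICC 0.5: 1.96/√2.33 = 1.28, giving 20%.
- Equal shares, ICC 0.7: 1.96/√2.87 = 1.16, giving 25%.
- Mostly few, ICC 0.7: 1.96/√2.15 = 1.34, giving 18%.
- Five in every patient, ICC 0.7: 1.96/√3.8 = 1.01, giving 31%.

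These agree with the simulation where both exist. The number of patients hardly matters; the ICC and the lesion counts do.

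**Effect on planning data.** Set the total variance of a lesion change to 1, with ICC 0.5 and three lesions in each patient. The pooled lesion SD is then 1. The variance of a patient mean is 0.5 + 0.5/3 = 0.667, so its SD is 0.82. The pooled SD is the larger one. The standard error goes the other way: the pooled variance of the mean is taken as 1/48 = 0.021, when it is 0.667/16 = 0.042, which is twice as large.

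**The case against.** The strongest reply is that the article never says lesions will be pooled. The wording is optional, it offers mixed models in the same clause, and it ties the choice to what is appropriate. Lesion count has one value per patient and suits a signed-rank test; SUV over several lesions suits a mixed model. On that reading nothing is wrong, and the unit of analysis may be set in a fuller protocol or SAP that is not shown. This stands as far as it goes: the article permits the faulty analysis and does not prescribe it. It does not remove the point, because the article itself pairs a lesion-level endpoint with a named test that is valid only on one value per patient, and defines no such value for SUV.

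A reader might infer three stronger things that the article does not support.
- That pooling would produce false declarations of flare. The section on criteria for the flare phenomenon and Table 1 define a flare by new lesions, a rise of at least 20% in uptake, or conversion to more than five lesions. No p-value enters, no alpha is set, and the analyses are descriptive.
- That p-values will certainly be far too small. The size depends on an ICC and a spread of lesion counts that are not given. Inflation is slight at ICC 0.1 and absent with one lesion per patient.
- That the next trial would be undersized. The pooled lesion SD exceeds the SD of patient means, so using it for a patient-level trial would tend to oversize it. Undersizing would need the further step of counting lesions as independent units.

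**Conclusion.** The point holds in conditional form. The plan leaves open an invalid analysis of the SUV part of its primary endpoint. If lesions were pooled as independent pairs, a nominal 5% test would reject a true null in about 6–9% of trials at ICC 0.1. At ICC 0.3–0.7 the figure is about 10–25% when lesion counts vary between patients. Five lesions in every patient is the extreme: 18% at ICC 0.3 and 31% at 0.7. All of this rests on assumed correlations, assumed lesion counts and normally distributed changes.

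Because the trial is exploratory, the consequence is limited to overstated evidence in any reported p-value, medians and IQRs weighted by lesion number, and planning data that mix variation between patients with variation between lesions. It is worth correcting because it concerns the primary endpoint and the trial's stated use, and because correction is almost free.

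**What to change.** In Statistical methods, state that:
1. Signed-rank tests, medians and IQRs for SUV use one summary per patient, for example the mean log ratio or the median percentage change over that patient's baseline lesions. Either choice will do if it is fixed in advance.
2. Lesion-level SUV data are analysed only with a mixed model with random effects for patient and for lesion within patient. The patient effect must act on the change from baseline. If log SUV at all three scans is modelled, this needs a patient-by-scan term, because a random patient intercept cancels out of every within-lesion difference and would leave the clustering untreated.
3. Between-patient and within-patient SDs of the change are reported separately for later powering.

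This needs no more patients, scans or data. The cost is a few sentences, and larger p-values than a pooled lesion analysis would show.

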### Data monitoring and auditing

An independent quality-monitoring official will oversee data integrity in accordance with GCP guidelines. Informed consent forms of selected participants will undergo check, and onsite monitoring will entail Source Data Verification to ensure alignment between data recorded in the CRFs and original source documents such as patient records and laboratory results. The intensity of this verification is related to the study’s risks. Monitoring activities will encompass verification of adherence to inclusion and exclusion criteria as well as scrutiny of the primary outcome measure, following a monitoring plan devised by the CRB. Additionally, the monitor will ensure that AEs and SAEs are reported promptly within legislative and regulatory timeframes. Throughout the study duration, the independent monitor will schedule four monitoring visits: the first visit after enrolling 2 patients, the second visit 6 months later, the third visit after 1 year, and finally, the close-out visit.

## Ethics and dissemination

The Medical Ethics Committee (METC) Amsterdam UMC has provided approval for the study protocol (2025–5 20 482-52-03), ensuring compliance with the principles outlined in the Declaration of Helsinki. The participant information sheet and informed consent form are provided as online supplemental material. Any protocol amendments during the study will be subjected to METC review and will be appropriately updated in the relevant registries. Written informed consent will be obtained from each patient prior to their participation. Findings from this study will be submitted for publication in a peer-reviewed journal, regardless of the outcome of this study, adhering to personal data privacy regulations, other applicable legislations, and the Central Committee on Research Involving Human Subjects (Centrale Commissie Mensgebonden Onderzoek). Furthermore, the study results will be disseminated at national and international conferences. All collected data will be archived in an open access digital repository in anonymous form.

## Discussion

The DARO-flare study marks a novel approach to using the darolutamide-induced flare phenomenon as a means to advance molecular imaging and staging methodologies in PCa. To our knowledge, this is the first prospective clinical study specifically designed to investigate and harness this biological effect for diagnostic purposes. Given the scarcity of prior research exploring the clinical translation of PSMA upregulation following short-term AR inhibition, a degree of uncertainty remains regarding both the magnitude and consistency of the flare phenomenon in humans. Consequently, we adopted a pilot, proof-of-concept study design that enables continuous evaluation of feasibility, safety and imaging response.

Previous studies investigating ARTAs, such as enzalutamide and apalutamide, have provided a biological foundation for this study. Both preclinical and clinical data have demonstrated that short-term ARTA administration can lead to upregulation of PSMA expression in PCa.^1^,^17^ The resulting transient increase in PSMA radiotracer uptake, described as the flare phenomenon, appears to occur within 9–14 days. However, evidence supporting this effect has been largely derived from small retrospective series and preclinical studies, and its translational potential for clinical imaging optimisation has not been established.^8^

Moreover, in contrast to enzalutamide and apalutamide, darolutamide exhibits a more unique pharmacokinetic profile, including lower penetration of the blood–brain barrier, minimal induction of major cytochrome P450 systems and limited potential for drug–drug interactions.^22 23^ Despite these distinctions, darolutamide acts through the same fundamental mechanism of AR antagonism and is therefore expected to elicit a similar PSMA-flare response.^22^ However, darolutamide has been reported to exhibit higher affinity for the AR and a longer dissociation half-life compared with enzalutamide and apalutamide, potentially contributing to similar or better upregulation of PSMA.^23^ Its favourable tolerability profile and restricted central nervous system exposure make darolutamide a suitable agent for short-term interventional studies of this nature, by minimising the likelihood of systemic side effects.

Another critical consideration is the biological and clinical interpretation of changes in PSMA uptake. Although increased SUV_max_ on PSMA PET/CT are widely assumed to reflect enhanced PSMA receptor expression, empirical evidence confirming this direct correlation remains limited. Previous studies have furthermore demonstrated that higher SUV_max_ values may correlate with clinically significant and more aggressive PCa.^24^ However, PSMA PET/CT may also show reduced sensitivity in specific histological subtypes, particularly ductal adenocarcinoma, which can be associated with false-negative findings due to low or heterogeneous PSMA expression.^25^ Therefore, both tumour biology and histological subtype may influence baseline uptake and the magnitude of any observed darolutamide-induced changes. As a result, SUV_max_ variations during the flare-phenomenon should be interpreted with caution, as they may reflect a combination of true receptor modulation and underlying characteristics. Additional translational work, including immunohistochemical validation and molecular imaging-pathology correlation, will be necessary to confirm that observed imaging changes correspond to actual modulation of PSMA protein expression and receptor density.

If the DARO-flare phenomenon can be verified and consistently reproduced, it may have several important clinical implications. Short-term pharmacological induction of PSMA expression could improve the sensitivity of PSMA PET/CT imaging, enabling more accurate detection of micro-metastatic disease and refinement of PCa staging. This enhanced sensitivity could influence therapeutic decision-making, particularly in patients with biochemical recurrence or oligometastatic recurrence, where precise delineation of disease burden determines eligibility for metastasis-directed therapy or systemic treatment initiation.

It is equally important to emphasise the exploratory nature of the present study. As a single-centre, phase I–II proof-of-concept study with a limited sample size, the DARO-flare study is not powered to assess clinical outcomes or long-term efficacy. Instead, it aims to establish biological feasibility, characterise the kinetics of PSMA upregulation and inform the design of future multicentre studies. The incorporation of randomisation between days 7 and 14 darolutamide exposure will provide valuable insight into the temporal dynamics of the flare response, allowing subsequent research to define the optimal imaging window.
